### Economic analysis

The economic evaluation will be conducted covering the period from baseline to 12-month follow-up and will take the NHS/personal social services perspective preferred by NICE.^22^ The intervention will be costed taking a bottom-up (micro-costing) approach^23^ using data collected on face-to-face contacts from IAPT records and accounting for the ratio of direct face-to-face to indirect non-face-to-face time. Data on indirect time, including preparation and supervision, will be collected directly from the therapists. Details of resources required to deliver the CBT-ts training and supervision will be provided by the TYPPEX research team. Use of all other health and social care services will be collected via a modified version of the adult service use schedule for early intervention (table 1) collected using REDCap data collection software at baseline (covering the last 3 months) and 3, 6, 9 and 12 months (covering the period since the last interview). Resource use data will be combined with nationally applicable unit costs.^24 25^ Productivity losses (applicable to sensitivity analyses only) will be calculated using the human capital approach by multiplying days off work for mental health reasons by the national average wage rate.^26^

Our primary economic analysis will be a cost-utility analysis using quality adjusted life years (QALYs) derived from the EuroQol measure of health-related quality of life (EQ-5D) based on complete case data. The EQ-5D-5L has been proposed as being more sensitive to change in mental health populations compared with the EQ-5D-3L.^27^ However, there is little evidence to support this hypothesis. Therefore, we will compare the psychometric properties of the 3L and 5L versions. The version of the EQ-5D used in this analysis will be dependent on analyses comparing the two. QALYs will be calculated by applying appropriate utility weights to EQ-5D health states^28^ and using the total area under the curve approach with linear interpolation between assessment points.^29^ A secondary analysis will additionally explore cost-effectiveness using the primary outcome measure: IAPT-defined recovery.

Costs and outcomes will be compared at the final follow-up point and presented as mean values by trial phase with SD. Mean differences in costs and 95% CIs will be obtained by non-parametric bootstrap regressions to account for the non-normal distribution commonly found in economic data.^30^ Incremental cost-effectiveness ratios (ICERs) will be calculated. Uncertainty will be explored using cost-effectiveness planes and cost-effectiveness acceptability curves based on the net-benefit approach.^31^ These curves are an alternative to CIs around ICERs and show the probability that one intervention is cost-effective compared with the other for a range of values that a decision maker would be willing to pay for an additional unit of an outcome. To provide more relevant treatment-effect estimates, all economic analyses will include adjustment for stepped-wedge cluster design, relevant baseline characteristics and other covariates,^32^ in line with the clinical analyses.

Sensitivity analyses will be conducted to explore the impact of missing data (using multiple imputation) and to explore cost-effectiveness from a broader perspective, including productivity losses because of time off work due to illness. Additionally, to assess the impact of missing data, we will compare those with economic data to the full sample included in the main clinical analysis to examine any potential biases in terms of demographic and clinical factors.

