**Methods and analysis:**

This is a multisite, stepped-wedge cluster randomised controlled trial. The setting will be IAPT services within three mental health trusts. The participants will be (1) 56–80 qualified IAPT cognitive behavioural therapists and (2) 600 service users who are triaged as appropriate for cognitive behavioural therapy in an IAPT service *and* have PE according to the Community Assessment of Psychic Experiences—Positive 15-items Scale. IAPT therapists will be grouped into eight study clusters subsequently randomised to the control-intervention sequence. We will obtain pseudonymous clinical outcome data from IAPT clinical records for eligible service users. We will invite service users to complete health economic measures at baseline, 3, 6, 9 and 12-month follow-up. The primary outcome will be the proportion of patients with common mental disorder psychotic experiences who have recovered by the end of treatment as measured by the official IAPT measure for recovery.

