**Trial registration number:**

ISRCTN93895792.

Strengths and limitations of this studyThe Tailoring evidence-based psychological therapY for People with common mental disorder including Psychotic EXperiences study will provide the first multisite, stepped-wedge cluster randomised controlled trial to investigate the clinical and cost-effectiveness of an intervention in the UK improving access to psychological therapies (IAPT) programme.The study intervention seeks to address the currently underserved needs of an important group of people accessing IAPT services.The stepped-wedge cluster design allows the intervention to be rolled out over time to all potential participants, while reducing operational and logistical challenges.The primary limitation is potential loss to follow-up, resulting in missing data for the secondary health economics outcome. This would challenge the internal validity of the conclusions drawn from the study.

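### The base-case cost-utility analysis is an undefined complete-case analysis, with multiple imputation only as sensitivity, although the plan names missing economic data as its main limitation

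*Protocol article*

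**What the plan says.** All of this is in the protocol article.

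- **Base case.** Under Economic analysis, the primary analysis is a cost-utility analysis with QALYs "derived from the EuroQol measure of health-related quality of life (EQ-5D) based on complete case data". QALYs are formed "using the total area under the curve approach with linear interpolation between assessment points".
- **Assessments.** The Abstract states: "We will invite service users to complete health economic measures at baseline, 3, 6, 9 and 12-month follow-up". Service use is recorded "at baseline (covering the last 3 months) and 3, 6, 9 and 12 months (covering the period since the last interview"). Procedures and Data management describe remote completion, online or by post.
- **Missing data.** Under the same heading: "Sensitivity analyses will be conducted to explore the impact of missing data (using multiple imputation"). The section also plans a bias check: "we will compare those with economic data to the full sample included in the main clinical analysis". It adds that "all economic analyses will include adjustment for stepped-wedge cluster design, relevant baseline characteristics and other covariates".
- **Stated limitation.** The Strengths and limitations box says: "The primary limitation is potential loss to follow-up, resulting in missing data for the secondary health economics outcome". It adds that this would threaten internal validity.
- **Size.** Sample size expects about 50% of those with routine data to consent to the economic measures, giving 150 per condition.
- **Linked data.** Data management and Ethics and dissemination say that the consented participants' economic data are linked to their clinical record. The footnote to table 2 says that PHQ-9 and GAD-7 are taken at every clinical contact.

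**The concern.** The plan identifies missing economic data as its chief weakness, then takes as base case the analysis most exposed to it. This is a stated choice, so it is not something left to an analysis plan that we cannot see.

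A complete-case analysis uses nothing from a person who returned some questionnaires but not all those required. It gives an unbiased incremental estimate only if, given the covariates in the model, being complete is unrelated to outcome. The document does not argue that this holds.

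The trial will hold information that could help. For many non-responders, end-of-treatment depression and anxiety scores and recovery status will still be in the linked clinical record. A complete-case analysis cannot use them well. They are measured after the intervention starts, so entering them as covariates in the effect model would remove part of the effect being estimated. Multiple imputation can use them as auxiliary variables without that penalty.

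At stake are the headline incremental cost-effectiveness ratio and acceptability curve. If the two planned analyses disagree, the plan has already committed to the complete-case one.

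**Working it through.** **1. Reproduce the plan's sample.** Inputs from Trial design and participants and Sample size: 8 clusters, 5 periods, at least 15 service users per cluster period, about 50% consent.

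- Clinical sample: 8 × 5 × 15 = 600.
- Economic sample: 600 × 0.50 = 300, or 150 + 150. This matches the plan.
- Per cluster period: 300 / 40 = 7.5 people before any drop-out.

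**2. Complete cases under assumed return rates.** The documents give no return rate, so the rates are assumptions. I take baseline as complete and require all four follow-ups. Two patterns bound the result for a common return rate r per wave:

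- independent non-response: 300 × r⁴
- the same people missing at every wave: 300 × r

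| Assumed return per wave (r) | Independent: 300 × r⁴ | Same people throughout: 300 × r |
|---|---|---|
| 90% | 300 × 0.656 = 197 | 270 |
| 80% | 300 × 0.410 = 123 | 240 |
| 70% | 300 × 0.240 = 72 | 210 |

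At r = 80% this leaves between 123 / 40 = 3.1 and 240 / 40 = 6.0 people per cluster period.

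**3. Returned questionnaires that go unused.** Under independence, 300 × 4 × r follow-up questionnaires come back, and complete cases supply 300 × r⁴ × 4 of them. The unused share is 1 − r³:

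- r = 90%: 1 − 0.729 = 27%
- r = 80%: 1 − 0.512 = 49%
- r = 70%: 1 − 0.343 = 66%

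If the same people miss every wave, the unused share of follow-up questionnaires is zero. Imputation then draws only on baseline and the linked clinical record.

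**4. What the other planned measures do.** Adjustment for baseline characteristics weakens the assumption needed, but it cannot bring in end-of-treatment status without the problem described above. The comparison with the full clinical sample shows whether those with economic data differ. Neither measure changes who contributes to the base-case estimate.

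**The case against.** The strongest objection is that complete case is undefined, so needing five assessments out of five is an inference. The plan's own construction could bridge a missed middle wave: utilities are interpolated linearly between assessments, and each service-use form runs back to the last interview. Someone who misses month 6 but answers month 9 might therefore still count as complete. A definition is also something an article may leave to a health-economics plan. This stands, and it is why the conclusion is conditional and the counts are given as a range. It does not remove the point: a missed month 12 cannot be bridged in this way, and the ranking of the two analyses is fixed in the text.

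Second, the plan is not silent on missing data. It has imputation, covariate adjustment and a comparison with the full sample, and nothing stops the planned imputation from using the clinical scores. That is also fair. The request is mainly to change which analysis is primary.

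Third, selection of responders that is similar in both phases need not bias the incremental estimate much. This is correct too, and the documents allow no estimate of bias in the ratio.

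Three stronger readings are tempting and not supported:

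- **That most of the economic sample will be lost.** The low counts are only the pessimistic end of assumed rates.
- **That those who keep responding will be the better recovered.** This is plausible, but the documents do not say it. The argument needs only that response may depend on outcome.
- **That the trial's main result is at risk.** The limitation is stated for the secondary economic outcome. The primary outcome comes from routine records.

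**Conclusion.** The point holds in conditional form. The plan makes a complete-case analysis its base case and relegates imputation to sensitivity, without justification and against its own statement of where the main weakness lies. If all four follow-ups are required, and return per wave is between 70% and 90%, the base case would rest on anything from 72 to 270 of the 300 consented. The width reflects two unknowns: the return rate and how far non-response repeats in the same people. A looser definition of complete case would lose fewer. The direction and size of any bias cannot be derived from the documents.

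The change is worth making because it costs little and uses data already to be held. It concerns a secondary outcome, so it is a recommendation and not a condition for the trial's validity. A reader might also infer that imputation would cure the self-selection of an opt-in half-sample. Imputation within the 300 does not. For the roughly 50% who do not consent, the planned comparison with the full clinical sample remains the only check.

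**What to change.** In the analysis plan or health-economics plan, before outcome data are examined:

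1. Make multiple imputation within the consented sample the base case. Include phase, period and team as terms in the imputation model. Do not fit separate models per phase if cells are too sparse; about 7.5 people per cluster period suggests they may be.
2. Use as predictors the baseline scores, all observed EQ-5D and cost data and, as auxiliary variables, the linked end-of-treatment PHQ-9, GAD-7 (or disorder-specific measure) and recovery status.
3. Define complete case, including how a missed intermediate wave is handled, and report that analysis as sensitivity.
4. Add one not-at-random scenario as a further sensitivity analysis.
5. Keep the comparison with the full clinical sample, and state that it addresses non-consent, which the imputation does not.

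The cost is a wording change and modest extra analysis, including a stated way of combining imputation with the planned bootstrap. No new data are needed. The price in assumptions is reliance on data being missing at random given the imputation model, which the not-at-random scenario is there to test.

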### Process evaluation analysis

Analysis of process evaluation data will be based on the constant comparative method.^33 34^ Practically, this will be achieved through multiple levels of analysis, systematically comparing data on different questions and from different sources (quantitative and qualitative) to achieve thematically ordered synthesis. Data analysis will take place after each stage of data collection so the analysis from each stage can inform data collection in the next. Some data analysis will also take place in parallel. The data will initially be subject to open coding using a combination of pre-selected questions and sensitising constructs identified from the literature. Codes will be increasingly grouped into higher-order explanatory categories through comparison and refinement in rounds of discussion and sense making. A set of overarching thematic categories will be agreed and used as a framework for further, more deductive, coding across the whole data set.

### Trial status

The trial was opened to IAPT service user recruitment in March 2021, with the first randomisation point scheduled for September 2021. Recruitment will continue until September 2023. The final 12-month follow-up is expected to be completed by October 2024.

## Ethics and dissemination

This study was approved by the South Central—Berkshire REC (REC reference 20/SC/0135 on 28 April 2020 and HRA on 23 June 2020). Subsequent amendments are shown in table 1.

The study is jointly sponsored by the University of Cambridge and Cambridgeshire and Peterborough NHS Foundation Trust. It was adopted onto the NIHR trial portfolio on 16 April 2020.

CBT-ts, including therapist training and supervision, is low risk for all participants. IAPT service users scoring above the CAPE-P15 thresholds for PE on whom data are being pseudonymously collected are under the care of the IAPT service for the duration of their participation and are subject to normal IAPT safety procedures. No specific risks, untoward incidents or adverse events related to CBT-ts are anticipated as the intervention aims to up-skill therapists rather than offering a new therapeutic intervention. This approach was supported by the results of a feasibility study as part of the wider TYPPEX research programme, during which no related serious adverse events were reported.

Safety outcome variables will be collected retrospectively each month from the routinely collected pseudonymous data. Aggregated safety information will be reported to the TYPPEX Data Monitoring and Ethics Committee throughout the randomisation condition. In addition, Principal Investigators, IAPT managers and therapists will be requested to report reports relating to TYPPEX by eligible participants to the trial team.

The clinical data generated during therapy (CAPE-P15, General Anxiety Disorder Assessment-7 (GAD-7), Patient Health Questionnaire-9 (PHQ-9) and anxiety disorder specific measure) is recorded as part of routine care and is used by this trial via an opt-out consent process. This is designed to remove the burden on IAPT therapists with respect to recruitment, and to ensure a representative sample.

A subgroup of service users are consented via an opt-in process to provide additional data outside of the clinical setting. This includes cost and quality of life health economic data, and follow-up clinical data at 12 months (see table 2). This data will be linked with their IAPT clinical record.

Results from this trial will be presented at national and international conferences, including the Schizophrenia International Research Society Conference and IEPA *Early Intervention in Mental Health Conference*. Dissemination will also occur through the submission of a primary article on the outcomes and several subsequent articles considering the effects of the intervention stratified by service user and therapist variables. Primary outcomes will be disseminated more widely as part of a theory-driven implementation plan, developing a community of practise including patients, the public, economists and systems engineers experienced in care pathway design and evaluation, in addition to stakeholders in the IAPT services.

The training materials will be shared electronically and will be widely available to the NHS.
